| Study period:
The combined study period will be 8 weeks. Each subject will receive placebo or ShK-186 subcutaneously twice weekly for 4 weeks followed by a 4 week follow-up period. Subjects will be observed in the clinical unit for at least two hours following each dose.

Planned Study Conduct Duration: approximately 5 months total (from enrollment of first subject to completion of follow-up for last subject); 8 weeks for each subject (first dose through End of Study, not including Screening).                                                                                                                                                                                                                                                                                                                                                                                                                                                                                                                                                                                                                                                                                                                                                                                                                                                                                                                                                                                                                                                                                    |

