**Biopsy Procedures (Day -7 to -1)**

- Review subject eligibility;
- Photographic documentation of psoriasis-involved body areas (see study manual);
- Identification and photographic documentation of lesional and nonlesional skin to be biopsied (at this visit and on Day 32) (see study manual for selection criteria);
- Identification and photographic documentation of target lesion for on-study assessment (not to be biopsied at any time, see study manual for selection criteria);
- Randomization (must occur before biopsy collection);
- Biopsy of lesional and non-lesional skin (see study manual for procedures and sample handling; subjects will be instructed to abstain from the use of emollients for 24 hours prior to the scheduled biopsy/photography);
- whole blood collection for biomarkers: PBMCs, plasma, serum and whole blood sample for RNA (TEMPUS™).

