### **6.3 Subject Withdrawal Criteria**

Subjects who meet all the inclusion criteria and have none of the exclusion criteria will be eligible to be enrolled into the study.

Subjects will be informed that they are free to withdraw from the study at any time and for any reason. The Investigator may remove a subject from the study if, in the Investigator's opinion, it is not in the best interest of the subject to continue the study. Subjects may be withdrawn if there are applicable safety or tolerability concerns on the part of the Investigator. Additionally, withdrawal of an individual subject will occur if any one of the following are met:

- Occurrence of an adverse event of Grade 3 or higher (CTCAE v4.0)
  - Grade 3 and greater laboratory abnormalities, that are
    - reproducible and sustainable (repeat laboratory test performed within 24-36 hours), and
    - clinically significant (according to the Investigator's discretion),
  - Grade 3 AEs that are clinically significant but clearly not related to study drug will be considered individually for withdrawal by the investigator, based on the clinical picture and logistical ability to manage the subject.
- Occurrence of a serious adverse event (SAE)
- Development of paresthesia/peripheral neuropathy symptoms that do not resolve prior to the next dose (at the discretion of the Investigator).

Notification of discontinuation will be made immediately to the Sponsor. In case of premature discontinuation of study participation, efforts will be made to perform all final study day assessments. The date the subject is withdrawn from the study and the reason for discontinuation will be recorded on the subject's Case Report Form (CRF). All dropouts will be followed until the resolution of all their AEs or until the unresolved AEs are judged by the Investigator to have stabilized.

Subjects that withdraw after receiving study drug will not be replaced. Subjects that withdraw prior to receiving study drug will be replaced and will receive a new study number.

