## **14.2 Safety Evaluations**

All subjects who receive study drug will be assessed for safety. The timing of the variables is presented in [Appendix A](#) and the variables will include:

- AE evaluations (all AE evaluations will include inquiry regarding the development of numbness/tingling or other symptoms/signs of neuropathy);
- Serious Adverse Events (SAE) evaluations;
- physical examination (including neurologic exam);
- vital signs (including temperature, respiratory rate, and supine blood pressure and pulse);
- clinical laboratory evaluations (including Chem-20, CBC, and UA; [Appendix H](#));
- antibody formation to ShK-186.

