#### 14.5.2 Recording Adverse Events

An AE is defined as any untoward medical occurrence experienced by a patient or healthy subject, whether or not considered drug related by the Investigator. A treatment emergent AE is an AE that is reported after a dose of study drug.

Adverse events/experiences are all:

- unfavorable changes in general condition;
- subjective or objective signs/symptoms;
- concomitant diseases or accidents;
- clinically relevant adverse changes in laboratory parameters observed in a subject in the course of a clinical study.

Adverse events/experiences comprise all disturbances of general health status, subjective and objective disease symptoms (including laboratory abnormalities), and accidents observed in the context of a clinical trial, irrespective of a possible causal relationship with the administration of the trial substance. Events occurring in the framework of a clinical trial during drug-free, and post-study drug periods, under placebo, or in a reference group receiving drug or non-drug therapy, are also to be designated as AEs.

All AEs, whether volunteered, elicited, or noted on physical examination, will be recorded throughout the study (*i.e.*, from the time of first injection on Day 1 until End of Study).

The severity of AEs that are clinical abnormalities, vital signs, and systemic issues will be

categorized according to the criteria presented in the Common Terminology Criteria for Adverse Events v4.0.

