#### **14.5.3 Reporting Serious Adverse Events (SAE)**

An SAE is any adverse drug experience occurring at any dose that results in any of the following outcomes:

- death;
- a life-threatening adverse drug experience (*i.e.*, places the subject, in the view of the Investigator, at immediate risk of death);
- inpatient hospitalization or prolongation of existing hospitalization;
- a persistent or significant disability/incapacity;
- a congenital anomaly/birth defect;
- important medical event that may require medical or surgical intervention to prevent one of the above outcomes.

Important medical events that may not result in death, be life-threatening, or require hospitalization may be considered SAEs when, based upon appropriate medical judgment, they may jeopardize the patient or subject and may require medical or surgical intervention to prevent one of the outcomes listed in this definition.

All SAEs, related or not, occurring during the study must be reported on an SAE Form within 24 hours of awareness to:

[figure not shown]

The CRO will notify the Sponsor within one (1) working day of original notification.

Sponsor will process and evaluate all SAEs as soon as the reports are received and will assess the relatedness of each SAE to the study treatment. For each SAE received, the Sponsor will make a determination as to whether the criteria for expedited reporting to relevant regulatory authorities have been met. Innovaderm will manage the expedited reporting of relevant safety information to Health Canada. The sponsor will manage the expedited reporting of relevant safety information to other concerned regulatory agencies in accordance with local laws and regulations.

IRBs and Investigators will be notified of SAEs in compliance with institutional and local requirements.

If a female subject or if a female partner of a male subject becomes pregnant during the study, the subject should inform the study site as soon as possible. No additional treatments shall be administered until a serum pregnancy test is performed and confirmed. Upon confirmation of the pregnancy, the female subject will be discontinued from the treatment portion of the study. Any confirmed pregnancy will be tracked and followed through outcome. While pregnancy itself is

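### AE recording opens only at the first injection, after the protocol's own pre-dose biopsies, and SAE reporting does not clearly cover the interval between them

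*Protocol*

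**What the plan says.** **AE window.** Section 14.5.2 records all AEs "from the time of first injection on Day 1 until End of Study". It offers this as the meaning of recording throughout the study. The same section also designates as AEs "Events occurring in the framework of a clinical trial during drug-free, and post-study drug periods".

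**SAE rule.** Section 14.5.3 begins "An SAE is any adverse drug experience occurring at any dose" and lists the qualifying outcomes. It then requires: "All SAEs, related or not, occurring during the study must be reported on an SAE Form within 24 hours". No start date is given.

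**Who is assessed.** Section 14.2 states: "All subjects who receive study drug will be assessed for safety".

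**What happens before dosing.** The Synopsis list for the Day -7 to -1 visit includes "Randomization (must occur before biopsy collection"), followed by biopsy of lesional and non-lesional skin. Section 14.1.2 describes the same visit.

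**Subjects lost before dosing.** Section 6.3 states: "Subjects that withdraw prior to receiving study drug will be replaced and will receive a new study number".

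**Duration.** The Synopsis gives "8 weeks for each subject (first dose through End of Study, not including Screening"). The same entry counts overall study conduct from enrolment of the first subject.

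**The concern.** The pre-dose biopsies are trial procedures, done solely for the protocol's purposes in subjects who have already been randomised. A complication in the days before the first injection precedes the only AE window that the protocol states, so a site following Section 14.5.2 literally would not enter it as an AE. That conflicts with the section's own inclusion of drug-free periods.

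For a serious complication, such as a hospitalised wound infection, the site must decide whether the 24-hour duty applies. The text does not settle this, and up to 4 centres may settle it differently.

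A subject who is biopsied and then not dosed is the hardest case. Exclusion criterion 11 (Section 6.2) bars acute infection within 7 days of baseline, and eligibility is reviewed again on Day 1. A wound infection that the investigator judges acute could therefore itself prevent dosing. The subject is then replaced, and nothing clearly requires a graded, causality-assessed AE record.

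**Working it through.** **1. The plan's own duration.** Day 57 minus Day 1 is 56 days, and 56 / 7 = 8.0 weeks. This agrees with the Synopsis, so the duration statement contains no error.

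**2. Length of the gap.** The biopsy visit is on Day -7 to -1 (Section 14.1.2), and there is no Day 0 (Figure 1 footnote). Day -1 to Day 1 is 1 day; Day -7 to Day 1 is 7 days. For the 24 planned subjects (Section 5.1):
- shortest: 24 × 1 = 24 subject-days
- longest: 24 × 7 = 168 subject-days

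**3. Biopsies before AE recording opens.** With 6 mm punches, each subject has one lesional and one healthy-skin biopsy before dosing and one lesional biopsy on Day 32 (Sections 13.2 and 14.1.2; Appendix A, note 6).
- before dosing: 24 × 2 = 48
- Day 32: 24 × 1 = 24
- share before AE recording: 48 / (48 + 24) = 48 / 72 = 67%

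If 4 mm punches are used, two lesional punches are taken at each time, but the number of healthy-skin punches is not fixed. Assuming one, the share is 3 / (3 + 2) = 60%. Assuming two, it is 4 / (4 + 2) = 67%.

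**4. Scheduled AE evaluations.**

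| Time | AE evaluation listed? | Source |
|---|---|---|
| Biopsy visit | No | Section 14.1.2; Appendix A |
| Day 1, before dosing | No | Section 14.1.3; Appendix A |
| Day 1, 30 minutes and 2 hours after dosing | Yes | Section 14.1.3; Appendix A |
| Later dosing days, before dosing | Yes | Sections 14.1.5 to 14.1.7; Appendix A |

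The schedule matches the window in Section 14.5.2. Day 1 is the only dosing day without a pre-dose AE evaluation.

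**5. Is a serious event between biopsy and first dose reportable?**

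- *Pointing to no:* the SAE definition presupposes a dose; the preceding section explains the study period for AE recording as starting at the first injection; Section 14.2 names only dosed subjects.
- *Pointing to yes:* SAEs are reportable whether or not related; drug-free periods are included in the AE definition; the sample AE question in Section 14.2.3 reaches back to Screening; overall conduct is counted from enrolment.

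Neither reading is ruled out. For AEs the window is explicit. For SAEs the text is ambiguous.

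**The case against.** The best defence is that the protocol has other ways of noticing these events.

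- Section 14.1.3 requires an interim history, a physical examination and an eligibility review before the first dose, so a dosed subject's wound complication would probably be seen. The AE question that can reach back to Screening would also elicit it.
- Section 6.3 is not limited to dosed subjects. It requires sponsor notification of discontinuation, a withdrawal date and reason on the CRF, and follow-up of dropouts' AEs.
- Section 14.1.9 asks subjects who discontinue early to complete the End of Study assessments, which include an AE evaluation.
- Section 14.2 promises assessment for dosed subjects without saying that others are left out.

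Much of this stands, and it defeats three stronger readings:

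- **That pre-dose SAEs are never reported.** Section 14.5.3 gives no first-dose start, and its wide wording on relatedness could include them.
- **That an undosed subject leaves no safety record.** Screening results (Section 17) and the withdrawal reason still go on the CRF, and replacement under a new number does not delete the first subject's record.
- **That the drug-safety data are selectively biased.** The primary objective (Section 4.1) concerns repeat doses of ShK-186, and a never-dosed subject carries no information on that.

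A reader might also infer a ceiling of 96 pre-dose punches (24 × 4). That assumes the healthy-skin punch doubles along with the lesional one, which the text does not fix.

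The defence does not close the gap in the rule. A history entry or withdrawal reason is not a graded, causality-assessed AE, and it does not trigger a 24-hour report. Follow-up of dropouts' AEs presupposes that an AE was recorded. An answer about a pre-dose event still falls outside the window in Section 14.5.2.

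**Conclusion.** The point holds for AEs as a stated rule and for SAEs as an ambiguity. Followed as written, Section 14.5.2 leaves complications of the trial's own biopsies outside AE recording for 1 to 7 days per subject, and it contradicts its own inclusion of drug-free periods. Section 14.5.3 does not say whether a serious event in that interval must be reported within 24 hours. A biopsied but undosed subject has a withdrawal reason on the CRF but no clear requirement for a full AE record.

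The size is 48 of 72 planned biopsies (67%) and 24 to 168 subject-days, assuming 24 subjects, 6 mm punches and a biopsy visit anywhere in the permitted window. These figures count opportunity. The protocol gives no complication rate, so the number of events at stake cannot be derived.

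The Synopsis duration is background only: it is arithmetically correct and does not set a reporting window. This is a contradiction in the protocol's own safety text, not a detail left to a statistical analysis plan. It does not undermine the design and is worth correcting because the correction is cheap.

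**What to change.** Reconcile the safety sections as follows:

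- **Section 14.5.2:** start AE recording no later than the pre-dose biopsy visit and continue to End of Study.
- **Section 14.5.3:** state the start of SAE reporting explicitly, no later than the biopsy visit, and from consent for SAEs related to trial procedures. Define an SAE as an untoward medical occurrence meeting a listed outcome, whether or not a dose has been given.
- **Section 14.2:** cover all subjects who are biopsied or dosed.
- **Section 14.1.3, the matching Synopsis list and Appendix A:** add an AE evaluation to the Day 1 pre-dose procedures.
- **Reporting:** flag events with onset before the first dose as pre-treatment and list them separately, outside the treatment-emergent tables. The flag is needed because Section 14.5.2 defines treatment emergence by when an event is reported. A biopsy complication first mentioned 30 minutes after dosing could otherwise be counted as treatment-emergent.

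The cost is protocol wording, one CRF flag, one more AE check at an existing visit and a few more AE entries. No visit or invasive procedure is added.

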**Exclusion Criteria:**

The following will exclude potential subjects from the study:

1. Erythrodermic, predominantly guttate, exclusively palmar/plantar, or generalized pustular psoriasis;
2. Current drug-induced or aggravated psoriasis (*e.g.*, a new onset of psoriasis or an exacerbation of psoriasis from beta-blockers, calcium-channel blockers, or lithium carbonate);
3. Use of the following concurrent systemic medications: corticosteroids, retinoids, cyclosporine, methotrexate, or biologic agents. The wash out period for these medications is 4 weeks or 5 half-lives prior to baseline, whichever is longer;
4. Use of concurrent topical medications (must be discontinued at least 2 weeks prior to baseline);
5. UVA or UVB therapy within 4 weeks of baseline;
6. The presence of uncontrolled hypertension, uncontrolled diabetes, clinically significant (uncontrolled) cardiovascular disease, uncontrolled asthma or reduced pulmonary capacity, or a history of seizure or other neurologic disorder;
7. Presence or history of pre-existing paresthesia or neuropathy;
8. Abnormalities on neurological exam at screening or baseline;
9. Clinically significant ECG abnormalities, in the opinion of the Investigator;
10. History of any cancer requiring systemic chemotherapy or radiation; individuals with a history of non-melanoma skin cancer, nonrecurring carcinoma in situ treated with laser or cryotherapy, or cervical cancer-in-situ, resected surgically with no evidence of disease, may be accepted on a case by case basis at the discretion of the Investigator;
11. The presence of acute infection or history of acute infection as judged by the Investigator within 7 days of baseline; additionally, oral temperature may not exceed 37.4 °C at baseline;
12. The presence of clinically significant laboratory abnormalities (chemistry panel of 20 analytes [Chem-20; fasted at least 4 hours], complete blood count [CBC], and urinalysis [UA]) as determined by the Investigator;
13. A positive hepatitis screen (Hepatitis BsAg or anti-HCV) or positive Human Immunodeficiency Virus

|                                                                                                                                                                                                                                                                                                                                                                                                                                                                                                                                                                                                                                                                                                                                                                                                                                                                                                                                                                                                                                                                                                                                                                                                                                                                                                                                                                                                                                                                                                                                                |
|------------------------------------------------------------------------------------------------------------------------------------------------------------------------------------------------------------------------------------------------------------------------------------------------------------------------------------------------------------------------------------------------------------------------------------------------------------------------------------------------------------------------------------------------------------------------------------------------------------------------------------------------------------------------------------------------------------------------------------------------------------------------------------------------------------------------------------------------------------------------------------------------------------------------------------------------------------------------------------------------------------------------------------------------------------------------------------------------------------------------------------------------------------------------------------------------------------------------------------------------------------------------------------------------------------------------------------------------------------------------------------------------------------------------------------------------------------------------------------------------------------------------------------------------|
| 
(HIV) antibody test ;
 

14. History of treated or untreated TB

15. Any history of anaphylaxis that is important in the view of the Investigator;

16. Participation in another clinical trial with receipt of an investigational product within 90 days of baseline (or 5 half-lives of the previous drug, whichever is longer);

17. History of alcohol abuse that is important in the view of the Investigator;

18. Positive drug screen for amphetamines, barbituates, benzodiazepines, cocaine, cannabis, methamphetamine, methylenedioxymethamphetamine, opiates or phencyclidine

19. Inadequate venous access that would interfere with obtaining blood samples;

20. Positive pregnancy test at screening or at baseline or current lactation (female subjects only);

21. Inability or unwillingness to comply with study restrictions, return for follow up appointments, or other considerations, in the opinion of the Investigator, which would make the candidate unsuitable for study participation.

                                                                                                                                                                                                                                                                                                                                                                                                                    |
| 
Investigational product, dosage, and mode of administration:
 
Following randomization, subjects will receive twice-weekly 0.3 mL SC doses of placebo (normal saline for injection) or ShK-186 as follows (9 total doses):
 
Group 1: Placebo SC injection twice weekly for 4 weeks (9 doses)
 
Group 2: 30 µg SC injection of ShK-186 twice-weekly for 4 weeks (9 doses, 270 µg total exposure)
 
Group 3: 60 µg SC injection of ShK-186 twice-weekly for 4 weeks (9 doses, 540 µg total exposure)
                                                                                                                                                                                                                                                                                                                                                                                                                                                                                                                                                                                                                                                                                                                                                                                                                                                                                                                                                                                     |
| 
Assessments:
 
Safety and Immunogenicity:
 
Vital signs, physical examinations, adverse events (AEs), serum chemistry, hematology, urinalysis, and antibodies to ShK-186.
 
Pharmacokinetics (abbreviated analysis to be performed by a secondary laboratory/Kineta):
 

• Maximum observed plasma concentration (<math>C_{max}</math>)

• Time to maximum plasma concentration (<math>T_{max}</math>)

• Trough plasma concentrations pre-dose on Day 15 and Day 57

 
Disease Activity:
 

• Change from baseline for Investigator and patient global assessments of psoriasis, DLQI and PDI

• Change from baseline for PASI score components (erythema, induration, and desquamation of skin of head, trunk and extremities)

• Change from baseline for % BSA involved

• Change from baseline in target lesion severity scores for target psoriatic lesion

 
Biomarker Analysis (to be performed by a secondary laboratory/Kineta):
 

• Change from baseline for psoriatic plaque histology

• Change from baseline for immune cell populations in psoriatic plaque by immunohistochemistry

• Change from baseline in cytokine expression in psoriatic plaque by qPCR

• Change from baseline for plasma cytokines and chemokines by Multiplex Immuno Assay (Luminex)

 |

- Change from baseline for IL-17A, F and A/F and other cytokines in serum by Single Molecule Counting technology (Singulex)
- Change from baseline in gene expression in whole blood samples (Tempus™)
- Change from baseline in peripheral T cell sub-populations by FACS

